## Abstract

**Introduction::**

Integrated care models aim to provide solutions to fragmentation of care by improving coordination. This study will evaluate the effectiveness of a new integrated care model (*Salut* *+* *Social*), which will promote the coordination and communication between social and healthcare services in southern Catalonia (Spain) to improve quality of life, adherence to treatment and access to medical services for patients with chronic conditions, and also to reduce caregiver burden. Additionally, we will evaluate the experience of caregivers, health professionals and social workers with the new model implemented.

**Methods and analysis::**

A clinical trial using mixed methodology will be carried out. The intervention consists of improving the coordination between the social and healthcare sectors during a 6-month period, by means of information and communication technology (ICT) tools that operate as an interface for the integrated care model. The study subjects are primary care patients with chronic health and social conditions that can benefit from a collaborative and coordinated approach. A sample size of 141 patients was estimated. Questionnaires that assess quality of life, treatment adherence, medical service and caregiver burden will be used at baseline and at 6, 9, and 12 months after the beginning of the study. The principal variable is quality of life. For statistical analysis, comparisons of means and proportions at different time points will be performed. A discussion group and semi-structured interviews will be conducted with the aim of improving the care model taking into account the opinions of professionals and caregivers. A thematic content analysis will be carried out.

**Ethics and dissemination::**

This study protocol has been approved by the Clinical Research Ethics Committee of the Fundació Institut Universitari per a la Recerca a l’Atenció Primària de Salut Jordi Gol i Gurina (code P17/100). Articles will be published in international, peer-reviewed scientific journals.

**Trial registration::**

Clinical-Trials.gov: NCT04164160.

## Introduction

1

One of the most significant demographic trends globally is the ageing of the population, with chronicity and multimorbidity increasing in high income countries. It is estimated that the percentage of the world's population older than 60 years will increase from 12% to 22% between 2015 and 2050.^[1]^ Health and social systems need to take the necessary steps to prepare for this demographic change in order to ensure adequate care.^[2]^

Chronic diseases are characterized by a long-term progression, limiting the quality of life of patients and caregivers, causing premature mortality and financial burden to families and society.^[3]^ Crucially, adults with multiple chronic conditions are the main users of healthcare services in all age ranges, and they account for two-thirds of healthcare spending. Consequently, increasing effectiveness of care in this group of patients should become a priority.^[4]^

Despite the differences between countries regarding the care of patients with chronic conditions, they all share similar challenges, including fragmented services, inefficient systems, poor quality, and spiralling costs.^[5]^ In recent years, new conceptual frameworks for the care of patients with chronic conditions have been developed, based on successful interventions such as the Chronic Care Model, which has achieved wide acceptance and dissemination and has inspired other models such as the Innovative Care for Chronic Conditions (ICCC)^[5]^ and the Expanded CCM.^[6,7]^

Integrated and person-centred care is a model increasingly incorporated into policies^[8,9]^ aimed to improve access, quality, continuity, effectiveness, and sustainability of healthcare systems.^[10]^ According to Shaw et al,^[11]^ integrated care is an organising principle for healthcare delivery that aims to optimize patient care by means of intensifying coordination between services. In this model, a collaborative and shared approach responds to patients’ needs.

The integration of social and healthcare services remains a challenge for healthcare systems in Europe and globally. A systematic review that analyzed the effectiveness of integrated care interventions in improving the quality of life for patients with chronic conditions concluded that Chronic Care Model interventions were beneficial, although the effectiveness increased with the number of components.^[12]^

Importantly, new healthcare technology is rapidly expanding, offering new opportunities for information sharing among departments and institutions and facilitating patients’ access to services.^[13–15]^

The principal objective of this study is to evaluate the effectiveness of a new integrated care model developed with the support of an information and communication technology (ICT) tool (named *Salut* *+* *Social*) in patients with chronic conditions, regarding quality of life and treatment adherence, medical service utilization and caregiver burden. The secondary objective is to analyse opinions and experiences of health and social professionals and caregivers with the new model implemented. The combination of quantitative and qualitative methodology, as established by the Medical Research Council,^[16–18]^ will provide a better evaluation of the intervention since it considers participants’ needs and environmental characteristics that might influence acceptability, adaptability, adherence, feasibility, and compatibility.

## Methods and design

2

A mixed methods study of 2 phases, following Medical Research Council guidelines^[16]^ on the evaluation of complex interventions, will be conducted between June 2019 and June 2020. Figure 1 shows the study flowchart.

**Figure 1 F1:**
[figure not shown]
Study flowchart.

### Setting and participants

2.1

Participants of the study are patients with chronic conditions and their informal caregivers from two primary care centres (PCC) of the *Institut Català de la Salut* (ICS) (*Ribera d’Ebre, Gerència Territorial Terres de l’Ebre, Catalunya*) that meet the health and social inclusion criteria.

#### Inclusion criteria (all criteria must be met)

2.1.1

Adult patients with at least one health and one social condition, as specified below:(a)Health condition, as registered in the electronic medical records of the ICS: complex chronic patient; advanced chronic disease; patient in the home care programme; dementia; neurodegenerative disease; stroke; other chronic diseases.(b)Social condition, according to the social services workstation from the *Ribera d’Ebre* district: dependence; home social services assistance; teleassistance systems assigned by the home support services.Knowledge of Spanish or CatalanAccepting participation in the study (informed consent signed by the patient or the caregiver).

#### Exclusion criteria

2.1.2

Institutionalized patients.Users with difficulties filling out or responding to questionnaires.

### Phase 1: effectiveness of the intervention

2.2

#### Study design and sample size

2.2.1

We will carry out a single group clinical trial to evaluate the effect of the implementation of a new integrated care model. The principal dependent variable is quality of life. In order to detect a difference of at least 3 units in the EuroQol-5D questionnaire, with 95% confidence and a power of 80%, the sample size should be at least of 141 subjects. Convenience sampling will be used.

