#### Statistical analysis

2.2.6

A descriptive analysis of all investigated variables will be provided, using means and standard deviations for quantitative variables and percentages with their confidence intervals for qualitative variables. We will evaluate if there is significant improvement in quality of life and a decrease in caregiver burden through a test of paired means, as well as improvement in treatment adherence using McNemar test of paired proportions before and after the intervention (after 6 months). Statistical significance is established at *P* ≤ .05, with a 95% confidence level.

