## Discussion

3

This is an innovative project in Catalonia, which aims to evaluate the effectiveness of a new integrated care model that takes into account the health and social conditions of patients with chronic conditions using ICT support. The project intends to strengthen the role of primary care services as promoter of integrative care for patients with chronic conditions.

This project is inspired by the current health policy published in the Health Plan of Catalonia 2016 to 2020, which recommends the collaboration between services and professionals, and suggests the transformation of the health system toward a more integral and person-centred care model. The Plan also promotes the use of ICT to facilitate the collaboration between institutions, care services and professionals, in order to provide better healthcare, avoid redundancies, and optimize resources.^[27]^

The study intends to respond to problems that arise from deficits in communication and coordination between social and health systems, such as the lack of a strategy regarding joint evaluation of patients, which generates duplication of information and slows down delivery of care. Since in our region the PCC do not have social workers, the health professionals need to contact municipal social workers to promote integration of care, underscoring the need for improvement in communication in this geographical area.

Because this study will be conducted in a small geographical area of southern Catalonia, the results obtained might not be replicable. However, we believe that our results will be of interest to other regions of Spain and also to the international community, since to date studies that evaluate the implementation of new models for integrating social and healthcare are scarce.^[28–30]^ Another limitation of the study might be the loss of participants due to worsening health and even death.

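### Phase 1 tests one group's change against zero, so its result describes change after implementation and cannot by itself show effectiveness

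*Protocol article*

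**What the plan says.** The aim is causal. The Introduction of the protocol article states: "The principal objective of this study is to evaluate the effectiveness of a new integrated care model". Phase 1 (section 2.2) carries effectiveness in its heading, and section 2.2.1 gives the design: "We will carry out a single group clinical trial to evaluate the effect of the implementation of a new integrated care model".

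The criterion is in section 2.2.6: "We will evaluate if there is significant improvement in quality of life and a decrease in caregiver burden through a test of paired means". Treatment adherence is compared by McNemar's test. The contrast is before versus after the intervention, at 6 months, with significance at P ≤ .05. No reference value other than zero change is named.

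On the course of disease, the Introduction says: "Chronic diseases are characterized by a long-term progression, limiting the quality of life of patients and caregivers". The inclusion criteria (section 2.1.1) admit, among others, patients with advanced chronic disease, dementia and neurodegenerative disease.

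The Discussion (section 3) names two limitations. One is the small geographical area. The other is attrition: "Another limitation of the study might be the loss of participants due to worsening health and even death". The lack of a comparator is not among them.

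**The concern.** A paired test answers whether the group's mean changed. It answers whether the model worked only if, without the model, the mean would have stayed where it was. The article has no concurrent or historical control, no repeated measurement before the intervention and no assumed untreated change (the change these patients would show without the model). Its own account of chronic disease gives a reason to doubt that this change is zero.

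If quality of life would otherwise have fallen, a model that slows the fall can yield no significant change, or even a significant worsening. If something other than the model were raising scores, a model with no effect could yield a significant improvement. In both cases the answer to the principal objective would depend on a quantity that the study does not measure. The same holds for caregiver burden and adherence, which are also tested before versus after.

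**Working it through.** **Inputs from the protocol article**
- Difference to detect: 3 EuroQol-5D units (section 2.2.1).
- Sample size 141, power 80%, confidence 95% (section 2.2.1).
- Test: paired means (section 2.2.6).

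**Assumptions, because the article does not give them**
- A two-sided test.
- The SD of the individual change.
- The untreated 6-month change, u.

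**Step 1: the plan's own figure.** For paired means, n = (SD × (z₀.₉₇₅ + z₀.₈₀) / 3)². No SD is stated, so 141 cannot be reproduced forwards. Solved backwards:

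SD = 3 × √141 / (1.960 + 0.842) = 35.62 / 2.802 ≈ 12.7 units.

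The exact t-based solution is 12.63, with standard error 12.63 / √141 ≈ 1.06. A one-sided reading would give 14.3.

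**Step 2: what the test sees.** With true benefit b, the expected mean change is b + u. The test sees only this sum. Then:

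P(significant improvement) = 1 − Φ(1.96 − (b + u)/SE)

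P(significant worsening) = Φ(−1.96 − (b + u)/SE)

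**Step 3: one row in full.** Take b = 3, u = -1 and the normal-theory SE of 12.71 / √141 = 1.070. Then (b + u)/SE = 2 / 1.070 = 1.87, and 1 − Φ(1.96 − 1.87) = 46%.

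**Step 4: results, n = 141.**

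| Untreated change u | b = 3: improvement | b = 3: worsening | b = 0: improvement | b = 0: worsening |
|---|---|---|---|---|
| -5 | <0.1% | 46% | <0.1% | 99.7% |
| -3 | 2.5% | 2.5% | <0.1% | 80% |
| -2 | 15% | 0.2% | <0.1% | 46% |
| -1 | 46% | <0.1% | 0.2% | 15% |
| 0 | 80% | <0.1% | 2.5% | 2.5% |
| +1 | 96% | <0.1% | 15% | 0.2% |
| +2 | 99.7% | <0.1% | 46% | <0.1% |

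The t-based SD gives the same figures to this rounding for significant improvement with b + u from 0 to 3.

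**Step 5: sensitivity to the SD.** For an SD of 10 to 15 units, the chance of detecting a true 3-unit benefit at u = -2 runs from 22% down to 12%. The chance of a false improvement at u = +2 runs from 66% down to 35%. The pattern does not hang on one SD.

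**The case against.** The other side has several fair points.

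- **The design is open and legitimate.** The article calls it single-group, and a before-after study of a service model with a qualitative phase is a recognised choice. This stands. The point is not that a control arm must be added. With the same assumed SD, a 1:1 comparison of change would need 2 × 141 = 282 per group, 564 in all, before any clustering by centre. Splitting 141 patients in two would give about 29% power.
- **The evidence for decline is general.** The Introduction's statement gives no rate and no 6-month figure. Section 2.1.1 also admits other chronic diseases, section 2.1.2 excludes institutionalised patients, and the Discussion says only that losses might occur. This stands too: the documents make zero untreated change doubtful but do not put a value on it.
- **Progression alone cannot create a false improvement.** A reader might infer that the protocol's remarks on progression mean the test can invent a benefit. They do not: decline can only hide a benefit or suggest harm. A reader might then point to the regional Health Plan in the Discussion as evidence that care is already improving. That text describes recommendations, and the same section reports gaps in local coordination and a lack of social workers in the centres. It does not establish an upward drift.
- **No stated rule equates P > .05 with lack of effect.** True. That reading comes from the effectiveness objective combined with the significance criterion.
- **Follow-up continues to 9 and 12 months, and the abstract mentions several time points.** This gives some information on the course after the 6-month intervention. Carry-over is possible, and it is not a comparator.
- **An analysis plan may exist.** It could add a sensitivity analysis, but it cannot recover a comparator that the design does not collect.

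**Conclusion.** The concern holds in a limited form and should be fixed. Phase 1 as written would present before-after change as evidence on effectiveness, with zero as the only reference, although the article itself gives reason to doubt that zero is what no effect looks like.

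On the stated assumptions, an untreated decline smaller than the 3-unit target is enough to cut the chance of detecting a true 3-unit benefit from 80% to 46% (at -1) or 15% (at -2). A decline of 3 units leaves 2.5%. An upward drift of 1 or 2 units would give a useless model a 15% or 46% chance of a significant improvement, against a nominal 2.5%. That second direction is conditional, since no such drift is shown.

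It would go too far to say that a model which slows decline will be reported as ineffective: at a decline of 1 unit it is still detected 46% of the time. The claim is that it can be missed. The SD, the sidedness and every untreated change are assumptions.

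**What to change.** 1. In the abstract, the objective and sections 2.2.1 and 2.2.6, state that Phase 1 estimates the mean change from baseline to 6 months after implementation. State also that P ≤ .05 alone will not be reported as effectiveness, nor P > .05 as lack of it.
2. In section 2.2.6, report the mean change with its 95% CI. Before analysis, fix a sensitivity table that subtracts a range of assumed untreated changes from the observed change and shows where the conclusion reverses. The sponsor should choose and justify the range, since the documents supply none.
3. Add the missing comparator to the limitations in section 3.

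The cost is revised wording and one table, with no new patients, visits or staff. The real price is a weaker headline claim, because the principal objective becomes an estimate of change. Effectiveness itself would still not be identified.

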#### Intervention

2.2.2

The intervention consists of promoting the coordination between the social and health sectors during a 6-month period by means of ICT tools that create an interface for the “*Salut* *+* *Social”* model, a new integrated care model. The ICT tools consist of a web application (app) and a mobile multicentre and multirole app, which maintains a constant communication flow between professionals from the different fields (primary healthcare, social services and hospitals), in order to share patients’ information and coordinate the actions that need to be implemented. The app also includes a suggestion box that healthcare and social services professionals can use to send suggestions for technical improvement, propose changes of processes and notify of app errors.

Nurses, general practitioners and social workers will participate in the intervention. Due to the lack of social workers in the primary care services of the study area, municipal social workers will be invited to participate in the study and will have assigned patients. Health professionals and social workers will inform users and their caregivers of available resources and grants, information on basic social services and on the Dependence Law.

The app should detect if the person requires social resources and will help allocate the necessary resource more effectively by joint action.

#### Training of health professionals and social workers

2.2.3

Before starting the study, participating professionals (nurses, general practitioners, and social workers) will receive training on aspects related to the use of the Salut + Social app, and how to access it from the webpage and the mobile app. A video with instructions will be posted in a YouTube channel.

#### Recruitment and data collection

2.2.4

Patients who meet the inclusion criteria will be selected by professionals and will be signed up to the app. In this step, clinical and social data of the patients will be automatically entered in the app and the professionals will propose coordinated actions with each patient. Next, patient and/or caregiver will attend a first interview with the nurse in charge of this task.

In the first interview, patients or caregivers will be asked to respond to the study questionnaires (ad hoc questionnaire for sociodemographic data, EuroQol-5D,^[19,20]^ Zarit questionnaire^[21,22]^ and Morisky-Green test^[23,24]^) and will participate in future care planning. If the nurse estimates that insufficient information for adequate integrated care exists, a joint visit with health professionals and social workers that can take place either in the health centre or at home could be requested through the app. Joint visits may be requested at any stage of the study whenever considered necessary.

Patients will receive an appointment to attend their PCC at 6, 9, and 12 months after their incorporation into the programme. During follow-up visits, patients or caregivers will be asked to respond to the same questionnaires, together with the IEXPAC questionnaire,^[25]^ which evaluates the experience of the chronic patient with the new care model.

Changes in the health and social needs of the patients and new interventions performed by any professional during the study period will be communicated through the app, enabling the coordination of all professionals involved.

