#### Outcomes and measurement instruments

2.2.5

The main result variable of the study is quality of life (EuroQol-5D). Table 1 shows the study variables, the measurement instruments and the timing of data collection.

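### Patient or caregiver may answer EuroQol-5D and Morisky-Green at any visit, so a change of respondent can enter the paired before-after comparison

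*Protocol article*

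**What the plan says.** Section 2.2.4 of the protocol article describes who is seen and who answers. For the start of the study: "Next, patient and/or caregiver will attend a first interview with the nurse in charge of this task". At that interview: "In the first interview, patients or caregivers will be asked to respond to the study questionnaires". The list that follows covers a sociodemographic form, EuroQol-5D, Zarit and Morisky-Green, all under the same either/or wording. For the visits at 6, 9 and 12 months: "During follow-up visits, patients or caregivers will be asked to respond to the same questionnaires", with IEXPAC added.

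Section 2.2.5 makes quality of life by EuroQol-5D the main outcome. Section 2.2.1 sets a single-group design and a target difference of 3 EuroQol-5D units with 141 subjects. Section 2.2.6 tests quality of life and caregiver burden by paired means and adherence by McNemar, before the intervention against 6 months.

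On the population, the health conditions in section 2.1.1 include "advanced chronic disease; patient in the home care programme; dementia; neurodegenerative disease; stroke", and consent may be "informed consent signed by the patient or the caregiver". Section 2.1.2 excludes "Users with difficulties filling out or responding to questionnaires". The Discussion expects some participants to be lost through worsening health or death.

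**The concern.** A paired test removes stable differences between people only if both members of a pair are measured in the same way. Here the rule as written allows a self-rating at baseline and a caregiver's rating at 6 months, or the reverse. The difference for that patient is then the change in the patient plus the gap between two raters.

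Three features make this matter. The population includes conditions in which a patient who could answer at baseline may be unable to at 6 months. There is no control group in which the same switching would occur and cancel. Caregivers are themselves informed about resources under the intervention (section 2.2.2), and their burden is an outcome, so a caregiver's rating of the patient may move for reasons other than the patient's state.

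At stake are the principal result and the adherence result. If respondent type is not recorded at the visit, it may not be possible to reconstruct it later.

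**Working it through.** **Inputs from the article.** Target difference 3 units; N = 141; 80% power; 95% confidence (all section 2.2.1). One group, paired comparison.

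**Inputs the article does not give, so assumed.** Score on a 0-100 scale (the article says only units); share of patients switching from self to caregiver, f = 10% to 20%; gap between caregiver and self rating, b = 5 to 10 units, of one sign; a two-sided test.

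**The plan's own figure.** The 141 cannot be reproduced because no standard deviation is stated. Solving the paired formula n = (SD × (z₀.₉₇₅ + z₀.₈₀) / 3)² backwards gives SD of change = 3 × √141 / (1.960 + 0.842) ≈ 12.7. This value is used below only to put the shift on a probability scale.

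**One-way switching.** Shift in mean change = f × b. The variance of the change becomes 12.7² + f(1 − f)b². The last column is the chance that a two-sided 5% test on 141 pairs rejects when the patients have not changed.

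| f | b | Shift (units) | Share of the 3-unit target | Rejection with no true change |
|---|---|---|---|---|
| 10% | 5 | 0.10 × 5 = 0.5 | 17% | 7.5% |
| 10% | 10 | 0.10 × 10 = 1.0 | 33% | 14.9% |
| 20% | 5 | 0.20 × 5 = 1.0 | 33% | 15.2% |
| 20% | 10 | 0.20 × 10 = 2.0 | 67% | 42.9% |

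The sign of b is unknown. If caregivers rate lower than patients, the same shift hides a benefit or produces an apparent decline.

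**Balanced switching.** If half of the switches go each way, the shift is zero and the variance becomes 12.7² + f × b². Power to detect 3 units, nominally 80%, is then:

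| f | b = 5 | b = 10 |
|---|---|---|
| 10% | 79.4% | 77.6% |
| 20% | 78.8% | 75.3% |

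**Adherence.** McNemar uses only discordant pairs. A pair that becomes discordant because a different person answered counts exactly like a real change. No figure can be put on this from the article.

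**Zarit.** This measures the caregiver's own burden, so self versus proxy is not the issue. The parallel requirement is that the same caregiver answers each time.

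**The case against.** The strongest reply is that this is a condensed article. Completion instructions, proxy wording and a respondent field often sit in a fuller protocol or data-collection manual. Table 1, which lists variables, instruments and timing, is not shown and might name respondents. The phrase about patients or caregivers also heads a mixed list: since Zarit concerns the caregiver, caregivers would have to be mentioned even if EuroQol-5D were always self-rated.

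Part of this stands. Allocation by instrument cannot be ruled out, and the article does not say that respondents will change. But the point does not rest on silence alone. The article states an either/or rule over all the instruments, states it again for follow-up, and pairs it with a within-patient test. Followed as written, that permits mixed pairs.

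It is also fair that every figure for switching and rater gap is assumed, and that switching mainly in patients who deteriorate is an inference from the eligibility list and the Discussion, not something the article reports.

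A reader might go further and infer that the eligibility lists contradict each other, because one admits "dementia; neurodegenerative disease; stroke; other chronic diseases" and the other excludes people who have difficulty answering. The text does not support that. An exclusion may narrow an inclusion list, and a patient with mild dementia can satisfy both. Section 2.2.2 speaks of users and caregivers as separate groups, which suggests that the exclusion means the patient. Because caregivers may consent and answer, it remains unclear whether a caregiver's ability to answer satisfies the criterion. That calls for a clarification.

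**Conclusion.** The point holds in this form: the stated respondent rule lets a change of rater enter the paired EuroQol-5D difference and the McNemar pairs for adherence, and a single-group design cannot separate it from the intervention effect. It should be corrected.

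Its size is not known. Under the assumed ranges (0-100 scale, one-way switching in 10-20%, gap of 5-10 units of one sign) the mean change moves by 0.5 to 2 units, or one sixth to two thirds of the target. Balanced switching does not move it and reduces power from 80% to between 75.3% and 79.4%. A reader might infer that the result will be biased in favour of the model; the article gives no switching rate, rater gap or direction, so only the possibility of bias, either way, is established. The conclusion would weaken if Table 1 or a fuller protocol assigns a fixed respondent to each instrument.

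**What to change.** - In section 2.2.4, set the respondent for EuroQol-5D and Morisky-Green for each patient at baseline: the patient, or a named caregiver using a proxy version. Require that respondent at every visit, and the same caregiver for Zarit throughout.
- Record respondent type for each questionnaire at each visit, including any switch that could not be avoided.
- In section 2.2.6, report the test of paired means and the McNemar test on all pairs and again on same-respondent pairs only. This keeps the planned tests and needs no new model.
- In section 2.1.2, say whether the exclusion refers to the patient's own ability to answer or is satisfied when a caregiver can answer. Dementia need not be removed from the inclusion list.

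The cost is one form field, one visit instruction and one clarified sentence. The downside is that switched pairs are lost from the sensitivity analysis: at the assumed 10-20% of 141, about 14 to 28 pairs (0.10 × 141 = 14.1; 0.20 × 141 = 28.2). If those are mainly patients who worsened, the restricted result describes a healthier subset, which is why both results should be shown.
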